### 2. Review and Oversight Requirements

#### a) Adverse Event – Reported By Phone Within 24 Hours

Adverse events requiring expedited reporting by phone within 24 hours (as described in the protocol) will also be reported by phone to the Clinical Trials Monitoring Committee administrator within one business day. Confirmation that all appropriate parties were notified will be done at this time. Hardcopies or electronic versions of NCI ADEERS form (#3500) and/or any other documentation available at that time will also be reviewed by the Committee Chair who will determine if immediate action is required. Within 10 working days all subsequent SAE documentation that is available will be submitted with a completed Mount Sinai SAE Evaluation Checklist to the Committee Chair who will determine if further action is required. All information will be tracked in the Mount Sinai School of Medicine Department of Radiation Oncology database.

If the AE occurs on a multiple-institutional clinical trial coordinated by the Mount Sinai School of Medicine Department of Radiation Oncology, the Research Coordinator will insure that all participating sites are notified of the event and resulting action within one working day of the determination.

#### b) Adverse Event – Reported within 10 Days

Adverse events requiring expedited AE reports in writing within 10 working days (as described in the protocol) will be sent to the Mount Sinai School of Medicine Department of Radiation Oncology Research Coordinator. Hardcopies or electronic versions of NCI ADEERS form (#3500) or other required forms will be submitted along with a copy of the SAE Evaluation Checklist. The Committee Chair will review these forms and determine if further action is required. This information will be tracked in the Mount Sinai School of Medicine Department of Radiation Oncology database.

If the AE occurs on a multiple-institutional clinical trial coordinated by the Mount Sinai School of Medicine Department of Radiation Oncology, the Research Coordinator will insure that all participating sites are notified of the event and resulting action within one working day of the determination.

#### c) Study Progress – Quarterly Review

Study progress assessment to determine whether accrual projections are being met and to determine if the trial should be continued based upon the likelihood of timely completion are reviewed at quarterly Clinical Trials Monitoring Committee meetings. Cumulative reports of adverse events requiring expedited reporting and any new adverse event requiring expedited reporting are also reviewed at the committee’s quarterly meetings.

An overall assessment of accrual, toxicities as described in the protocol, and responses will enable the committee members to assess whether significant benefits or risks are occurring that would warrant study closure. This information is provided by meeting minutes, internal audit and/or response review reports. The committee may request external DSMB reports or further information from the Study Chair.

The Clinical Trials Monitoring Committee recommendations for modifications to the trial are forwarded to the Institutional Review Board. The Study Chair is notified of this recommendation in order that he/she may alert all investigators, at the Mount Sinai School of Medicine Department of Radiation Oncology and at external sites involved in the trial, about the potential action. At this time the Study Chair may submit to the Institutional Review Board additional information that could affect the Committee’s decision. The Institutional Review Board will notify the Study Chair if they concur with the Clinical Trials Monitoring Committee recommendations, including suspension or closure. The Study Chair will notify all investigators involved with the study at the Mount Sinai School of Medicine Department of Radiation Oncology and external sites, the IRB, the sponsor and the funding agency and provide written documentation of these notifications to the Institutional Review Board.

#### d) Review of Adverse Event Rates

Once a month, adverse event rates will be monitored utilizing the Mount Sinai School of Medicine Department of Radiation Oncology Clinical Trials database. If any study has had two or more of the same AE reported in a month or more than six of the same AE in six months, the CTMC Chair will review the summary of SAEs, discuss events with Study Chair, and conduct a more detailed review with the Study Chair or the external DSMB if warranted. The Committee Chair will determine if further action is required. If this occurs on a multiple-institutional clinical trial coordinated by the Mount Sinai School of Medicine Department of Radiation Oncology, the principal investigator will insure that all participating sites are notified of the resulting action.

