  - All patients who have met the eligibility criteria will be included in the main analysis of the response rate. Patients in response categories 4 – 8 will be considered as failing to respond to treatment (disease progression).
  - All individual lesions will also be recorded as CR, PR, SD, or PD.
  - Overall survival is the time from the date of first study treatment until death from any cause.

Overall survival and progression-free survival (PFS) will be calculated using the Kaplan-Meier (1958) estimator.(40) Median survival times and their associated 90% confidence intervals will be derived using the method described in Brookmeyer and Crowley (1982).(41)

The percentage of patients with complete responses and the percentage with complete or partial responses will be calculated and confidence intervals derived. The pattern of failures (local or distant) will be summarized. Adverse effects will also be tabulated by type and level of severity. Potential prognostic variables, such as number of lesion sites at baseline, will be examined by fitting Cox (1972) regression models for progression-free and overall survival times.(42) Given the sample size, only univariate analysis will be performed.

- Accrual Rate and Study Duration
  - The estimated accrual will depend on toxicity encountered, but we anticipate enrolling 50-65 patients.
  - We anticipate enrolling 1-3 patients per month.

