Once a month, adverse event rates will be monitored utilizing the Mount Sinai Department of Radiation Oncology Clinical Trials database. If any study has had two or more of the same AE reported in a month or more than six of the same AE in six months, the CTMC Chair will review the summary of SAEs, discuss events with Study Chair, and conduct a more detailed review with the Study Chair or the external DSMB if warranted. The Committee Chair will determine if further action is required.

If this occurs on a multiple-institutional clinical trial coordinated by the Mount Sinai Department of Radiation Oncology, the Safety Coordinator will insure that all participating sites are notified of the resulting action.

EXPEDITED REPORTING OF ADVERSE EVENTS

Depending on the nature, severity, and attribution of the event an ADR report will be phoned in, submitted in writing, or both according to Tables below. Telephoned Adverse Events must also be reported by phone to the Mount Sinai Department of Radiation Oncology Clinical Trials Monitoring Committee within one working day of the event. All adverse events must also be reported to the Mount Sinai IRB, and any sponsor/funding agency not already included in the list.

| Telephone reports to:  (Investigator: Insert names and phone numbers for required notifications) •   1. Mount Sinai Clinical Trials Monitoring Committee Administrator [contact]- within one working day of the event |
| --- |
| Written reports to:  (Investigator: Insert names, fax numbers, and addresses for required notifications)   1. Mount Clinical Trials Monitoring Committee Administrator –   [contact] or deliver to Clinical Trials Office, Division of Hematology Oncology at Atran 2nd Floor   1. Mount Sinai IRB – Copy of final written report to Sponsor. |

| TABLE 1 | | | |
| --- | --- | --- | --- |
| Summary Of Reporting Requirements For Adverse Events On Trials Where The Investigator Holds IND | | | |
| EXPEDITED REPORTING FOR PHASE I STUDIES | | | |
| Unexpected Event | | Expected Event | |
| GRADES 2 - 3  Attribution of Possible, Probable, or Definite | GRADES 4 and 5  Regardless of Attribution | GRADES 1 - 3 | GRADES 4 and 5,  Regardless of Attribution |

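### Appendix 3's six-month adverse-event limb (more than six) can never fire before its one-month limb (two or more), so a steady once-a-month event never meets the trigger

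*Protocol*

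**What the plan says.** Protocol, Appendix 3, I.B.2.d (Review of Adverse Event Rates), sets a periodic screen: "Once a month, adverse event rates will be monitored" from the departmental trials database. The screen has two limbs joined by OR: "two or more of the same AE reported in a month or more than six of the same AE in six months". If either is met, "the CTMC Chair will review the summary of SAEs, discuss events with Study Chair", with a more detailed review if warranted. The Policy and Procedures part of the same appendix repeats the rule with the same thresholds.

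On accrual, Section 16 states "We anticipate enrolling 1-3 patients per month". The synopsis plans 52 patients, with first enrolment estimated for 1/1/2007 and last for 9/1/2011.

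Other safety review is described elsewhere. Section 15 and Appendix 3 provide for biweekly meetings at which toxicities are discussed. Appendix 3, I.B.2.a and b, has the Committee Chair look at expedited events individually. Under I.B.2.c the committee meets quarterly: "Cumulative reports of adverse events requiring expedited reporting and any new adverse event requiring expedited reporting are also reviewed". Sections 10 and 16 give the phase I 3+3 rule on dose-limiting toxicities.

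**The concern.** In a two-limb count rule, the longer window normally earns its place by catching events that build up too slowly for the shorter one. Here the thresholds are set so that the longer window has nothing left to catch. One event in each of six months totals six, which is not more than six. The next event that would bring the six-month total to seven must fall in a month that already holds one, and that meets the one-month limb anyway.

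At stake is a screen that appears to cover both clustering and slow accumulation but covers only clustering. With one to three patients entering per month, a toxicity affecting a sizeable fraction of patients may well appear about once a month. That pattern can continue for the whole trial without meeting this trigger.

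**Working it through.** **Inputs.** One-month limb: at least 2. Six-month limb: more than 6, so at least 7. Both are from Appendix 3, I.B.2.d. Accrual of 1 to 3 per month is from Section 16. The 52 patients and the dates are from the synopsis. The event probability of one third and the timing models below are assumptions; the protocol gives no such figures.

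**1. Redundancy.** Let x1, …, x6 be the monthly counts of one event. If the one-month limb has not fired, every x is at most 1, so the total is at most 6 × 1 = 6, which is not more than 6. Conversely, a total of 7 forces some month to hold at least 7/6, rounded up to 2. As a check, all vectors with 0 to 7 events per month were enumerated: 261,220 have a total above six, and none of these has every month at one or below. In 100,000 simulated 24-month sequences with monthly checks, the six-month limb fired in 44,141 and never before the one-month limb.

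**2. Steady recurrence.** One event per month for 24 months gives a monthly maximum of 1 and a six-month maximum of 6. Neither limb fires.

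**3. Accrual.** 1/1/2007 to 9/1/2011 is 56 months, and 52/56 = 0.93 patients per month on average.

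**4. How often the existing rule flags within six months.** Take a mean of one patient per month, at most one event per patient, and event probability p = 1/3.
- Exactly one entry per month, event in the entry month: no month can hold two, so the chance is 0%.
- Poisson entry, event in the entry month: monthly events are Poisson with mean 1/3. P(at most one in a month) = e^(−1/3) × (1 + 1/3) = 0.9554. The chance of a flag is 1 − 0.9554^6 = 0.24.
- The same Poisson model with p = 1: P(at most one) = 2e^(−1) = 0.7358, and 1 − 0.7358^6 = 0.84.

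**5. What a lower six-month count would add.** Of the 2^6 = 64 patterns with at most one event per month, the number that would fire is 0 at seven or more (the current rule), 1 at six or more, 7 at five, 22 at four and 42 at three.

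For p = 1/3, the chance of a flag within six months with both limbs in force is as follows. With exactly one entry per month it is the upper tail of Bin(6, 1/3). With Poisson entry it is 1 − e^(−2) × Σ C(6,k)(1/3)^k, summed from k = 0 to one below the threshold.

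| Six-month limb | Exactly one entry per month | Poisson entry, mean 1 |
| --- | --- | --- |
| 7 or more (current) | 0% | 24.0% |
| 6 or more | 1/729 = 0.1% | 24.0% |
| 4 or more | 73/729 = 10.0% | 1 − 0.1353 × 5.407 = 26.8% |
| 3 or more | 233/729 = 32.0% | 1 − 0.1353 × 4.667 = 36.8% |

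**6. Cost in extra reviews.** For one event type with a 5% probability, a limb of three or more acting alone would fire in P(Bin(6, 12, 18; 0.05) ≥ 3) = 0.2%, 2.0% and 5.8% of six-month periods at exactly 1, 2 and 3 patients per month. With many event types screened, the total is higher.

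**The case against.** The strongest reply is that the redundancy matters little because the one-month limb works and the screen is one layer among several. Much of this stands. Toxicities are discussed at biweekly meetings, expedited events are reviewed individually and cumulatively each quarter, and in phase I the 3+3 rule counts dose-limiting toxicities per dose level whatever the calendar month. The screen leads to a Chair review and does not itself stop the trial. But the 3+3 rule covers only phase I and, under Section 16, events within 30 days of starting radiation. The other layers carry no numerical threshold on event rates.

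Three stronger readings are tempting, and the documents do not support them:

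- A reader might infer that at one patient per month the rule stays silent even if every patient is harmed. That needs exactly one entry every month and onset only in the entry month. The protocol fixes neither, and patients stay on maintenance drug with continuing assessment, so events can coincide. With Poisson entry and every patient affected, the rule flags in 84% of six-month periods.
- A reader might infer that firing depends on accrual speed rather than on harm. At fixed mean accrual the chance rises from 24% to 84% as the event probability goes from one third to one. Any absolute-count trigger also varies with accrual, including a repaired one.
- A reader might see a separate fault in a trigger that counts AEs while the Chair reviews a summary of SAEs. The same sentence has the Chair discuss the events with the Study Chair and review further if warranted, so this does not stand alone as an error.

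Two smaller points are fair. The appendix is a departmental plan covering any study and states no purpose for the six-month limb, so its intended role is inferred. And if one limb used calendar months while the other used a rolling window, an exception exists: seven events in seven calendar months, for example 31 January to 15 July, a span of 166 days. The protocol describes no such mixed windows.

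**Conclusion.** The point holds as a fault in a stated threshold. When both limbs use the same months, the six-month limb adds nothing, and the trigger is simply two of the same event in one month. This is exact and needs no assumption about accrual or event probability. A steady once-a-month event never meets the trigger, although it is not thereby unseen, because the other reviews remain.

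The practical size is less certain. At a mean of one patient per month and a one-third event probability, the existing rule flags within six months with a chance between 0% and about 24% under the two timing models examined. Those figures are illustrative and assume at most one event per patient; repeated events on maintenance treatment would raise them. The fault is worth correcting because it sits in a safety rule and the correction is cheap. It does not show that the trial lacks safety monitoring.

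**What to change.** In both places in Appendix 3 (I.B.2.d and the matching paragraph under Policy and Procedures), lower the six-month limb to a count of six or fewer and keep the one-month limb unchanged. Six or more is the minimum that lets the limb act alone, but it catches only the pattern with an event in every one of the six months. A count such as three or four catches slower accumulation, at the price of occasional extra Chair reviews. The sponsor should choose the value and state it. The present finding gives no ground for adding a severity-grade restriction.

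The cost is one sentence in two places. No new data are needed, since the database is already checked monthly. Because the appendix is a departmental plan, the department would need either to amend it for all its studies or to state the changed count as specific to this protocol.

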9.10 Dose Modifications for Sutent(Applies only to phase II)

Dose modification of Sutent can be secondary to any grade 3 toxicity related to Sutent according to the judgment of the treating physician. When toxicities eliciting dose modification occur, Sutent will be temporarily discontinued but restarted at the next lower dose level when the toxicity has resolved to grade 2 or lower. In the event of hospitalization for reasons other than drug toxicity, patients should be directed to continue trial drug at the discretion of their physician. The principal investigator should be notified immediately of any compliance issues that arise in the course of the trial. If a patient still experiences dose-modifying toxicities despite drug holiday and reduced dose schedule, the patient, if benefiting from treatment, should stop receiving Sutent and continue radiation.

The following toxicities, in addition to any other toxicity as judged by the treating physician, merit temporary discontinuation should be considered dose-limiting toxicity:

1. Any CTC grade 3 or 4 non-hematopoietic adverse event that the investigator considers consistent with a drug-related toxicity;

2. Any CTC grade 4 hematopoietic adverse event that the investigator considers consistent with a drug-related toxicity;

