**Table 1. Phase I Dose Levels**

| **Dose Level** | **Radiation Dose** | **Sutent Dose** |
| --- | --- | --- |
| 1 | 40 Gy in 10 fractions | 25 mg PO QD |
| 2 | 40 Gy in 10 fractions | 37.5 mg PO QD |
| 3 | 50 Gy in 10 fractions | 37.5 mg PO QD |
| 4 | 50 Gy in 10 fractions | 50 mg PO QD |
| 5 | 60 Gy in 10 fractions | 50 mg PO QD |

.

Phase I dose escalation will proceed according to a “3+3” design. After 3 patients have been treated on each dose level, they will be followed for at least 30 days. If 0 of 3 patients have DLTs, the dose will be escalated to the next dose level. If ≥2 of 3 patients have DLTs, dose escalation will be terminated and the next lowest dose level will be declared the maximal tolerated dose for Phase II evaluation. If 1 of 3 patients has a DLT, then three more patients will be treated at the same dose level and if the incidence of DLT among six patients is < 2 of 6, the dose will be escalated to the next level for that site.

- Grades 3-5 non-hematological toxicities (excluding nausea, vomiting, and alopecia) and Grade 4-5 hematological toxicities will be referred to as dose limiting toxicities (DLT).
  - Esophagitis and mucositis are very common side effects with radiation therapy and grade 3 side effects can be seen after palliative courses of radiotherapy. Therefore, grade 3 mucositis or esophagitis lasting ≤ 7 days will **not** be considered a DLT. If the grade 3 mucositis or esophagitis lasts > 7 days, it will then be considered a DLT.
- The recommended phase II dose will be 1 dose level below the defined MTD or at the maximum tested dose if the MTD has not been reached.

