  - Once the appropriate AE documents have been received, the principal investigator forwards these to the IRB (Mount Sinai only), affiliate institutions if applicable. A copy will be forwarded to the appropriate Research Nurse.
- Data Safety and Monitoring
  - Data Safety and Monitoring will occur at the biweekly Mount Sinai School of Medicine, Department of Radiation Oncology phase I/II quality assurance meetings, which are lead by the department chairman ([name].) and include a medical oncologist ([name].) and patient advocate. At each meeting, all active studies will be reviewed for safety and progress toward completion. Toxicities and adverse events will be reviewed at each meeting and a Data Safety and Monitoring form will be completed for each protocol and signed by either the principal investigator, the chairman of the department or by his designate if the chairman is not available.

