**16. STATISTICAL CONSIDERATIONS**

- Phase I: The primary objectives are to determine the maximum tolerated dose (MTD) and dose limiting toxicity (DLT) of extracranial stereotactic radiation therapy in combination with Sutent when given to all sites of involved disease in patients with metastatic cancer.
- For dose escalation purposes, the major endpoint will be dose-limiting toxicity occurring within 30 days after the start of radiation therapy.
- Dose limiting toxicity is defined as follows: Grade 3-5 non-hematological toxicities (excluding nausea, vomiting, and alopecia) and Grade 4-5 hematological toxicities.
  - Esophagitis and mucositis are very common side effects with radiation therapy and grade 3 side effects can be seen after palliative courses of radiotherapy. Therefore, grade 3 mucositis or esophagitis lasting ≤ 7 days will not be considered a DLT. If the grade 3 mucositis or esophagitis lasts > 7 days, it will then be considered a DLT.
- The MTD for a specific area will be exceeded if 2 or more patients out of 6 (or a third or more) with disease at that site experience DLT at that dose. The dose immediately below will be recommended for further study.
- Phase II: *(Includes 3 to 6 patients from Phase I MTD):* The median progression free survival with optimal chemotherapy alone for the 4 most common tumor types (lung, breast, prostate and colorectal) ranges from 2.2 to 10.6 months, depending on primary tumor site and degree of pretreatment. Therefore, we will assume a median time to progression of 6.4 months (standard deviation 3.2 months) with chemotherapy alone. With 38 patients, this study has 87% power (α=0.05) to detect a 25% increase in time to progression. Also the 2 year freedom from progression is <5% with chemotherapy therapy and this study has 70% power (α=0.05) to demonstrate a 10% absolute increase in 2 year progression-free survival.
  - All patients included in the study will be assessed for response to treatment, even if there are major protocol treatment deviations or if they are ineligible (intent-to-treat population). Criteria described in Section 10 will be used to assign each patient to one of the following response categories: 1) complete response, 2) partial response, 3) stable disease, 4) progressive disease, 5) early death from malignant disease, 6) early death from toxicity, 7) early death because of other cause, or 8) unknown (not assessable, insufficient data).

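### Phase II safety oversight is substantial, but nothing counts all patients with a DLT against a limit or requires enrolment to pause; a short rule in Section 16 would add both

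*Protocol*

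**What the plan says.** **Phase I.** Section 10 clears a dose level on 0 of 3, or fewer than 2 of 6, patients with a DLT. Section 16 ties the DLT endpoint to escalation: "For dose escalation purposes, the major endpoint will be dose-limiting toxicity occurring within 30 days after the start of radiation therapy". Its limit of two of six, or a third, is worded per anatomical area and sits under Phase I.

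**Phase II.** Section 16 plans 38 patients and says of them "Includes 3 to 6 patients from Phase I MTD". It sets no toxicity limit; adverse effects are tabulated. Section 9.10, which applies only to phase II, lists drug-related events that "merit temporary discontinuation should be considered dose-limiting toxicity", but the action is to hold, reduce or stop that one patient's Sutent.

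**Dose carried forward.** Section 10 states: "The recommended phase II dose will be 1 dose level below the defined MTD", or the highest tested level if no MTD is reached. The synopsis treatment plan agrees. The phase II dose statements in Sections 8, 9.2 and 9.9 name the MTD itself.

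**Oversight.** Section 15 says of the biweekly quality-assurance meetings: "Toxicities and adverse events will be reviewed at each meeting". Appendix 3 adds a monthly adverse event (AE) rate screen, quarterly review by the Clinical Trials Monitoring Committee (CTMC), interim CTMC meetings for urgent safety matters, and chair review of expedited events. On the quarterly review it says: "An overall assessment of accrual, toxicities as described in the protocol, and responses will enable the committee members" to judge whether closure is warranted. Cumulative reports of expedited events are part of that review. The monthly screen is triggered by "two or more of the same AE reported in a month or more than six of the same AE in six months", after which the chair decides whether anything further is needed.

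**The concern.** The synopsis and Section 2c say that there are no clinical data on Sutent with radiation. Most patients in the trial will receive the combination in phase II, on the strength of 3 to 6 patients at that level. Phase I has explicit DLT counts with fixed consequences. Phase II keeps a DLT label but attaches no count and no consequence for enrolment.

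The one numerical trigger does not fill that gap. Radiation may go to up to five sites anywhere in the body, so DLTs may differ in kind. Four unlike DLTs in the first 8 patients (4/8 = 50%) would not be repeats of one AE and would meet no stated criterion, although the meetings would see them.

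The cumulative reports also have a gap. In the expedited-reporting tables of Appendix 3, expected grade 1 to 3 events need no expedited report unless they led to hospitalization. An expected grade 3 non-haematological toxicity managed without admission is generally a DLT under Section 16, yet need not appear in the cumulative reports. It reaches the CTMC through minutes and summaries, uncounted.

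At stake is how surely, and how soon, enrolment halts if phase I cleared a too-toxic level by chance.

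**Working it through.** The protocol gives no phase II toxicity limit to reproduce. Its phase II size is taken as stated. A one-sample z-test reproduces the power quoted for it: Φ(1.6/3.2 × √38 − 1.96) = 0.869, against 87%.

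**1. Further patients (Section 16).** 38 − 6 = 32 to 38 − 3 = 35.

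**2. How firmly the dose is cleared (Section 10).** The one-sided 95% upper limit for the DLT rate is 1 − 0.05^(1/3) = 63% after 0/3. It is 58% after 1/6 (the 0.95 quantile of Beta(2, 5)). For a true DLT rate p, a level that is reached is cleared with probability c(p) = (1−p)³ + 3p(1−p)⁵:

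| p | 0.20 | 0.25 | 1/3 | 0.40 | 0.50 | 0.60 |
|---|---|---|---|---|---|---|
| c(p) | 0.709 | 0.600 | 0.428 | 0.309 | 0.172 | 0.082 |

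These apply if phase II uses the highest cleared level. If it is one level lower, both levels must clear:
- True rate 40%, with 40–50% assumed above: 0.309 × 0.309 = 0.096 down to 0.309 × 0.172 = 0.053.
- True rate 50%, with 50–60% assumed above: 0.172 × 0.172 = 0.030 down to 0.172 × 0.082 = 0.014.

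**3. What each layer does in phase II.**

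| Layer | Pools unlike DLTs? | Numerical limit? | Pause required? |
|---|---|---|---|
| Biweekly meeting (Section 15; App. 3, I.B.1.b) | Toxicities discussed, no count set | No | No |
| Monthly screen (App. 3, I.B.2.d) | No, same AE only | Yes | No, chair review |
| Quarterly CTMC (App. 3, I.B.2.c) | Yes, for expedited events | No | No, may recommend suspension or closure |
| Interim CTMC meetings (App. 3, I) | Not specified | No | No |
| Chair review of expedited events (App. 3, I.B.2.a–b) | One at a time | No | No, chair may act |
| Section 9.10 | One patient at a time | No | No |

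**4. An example boundary.** Pause when the posterior probability that the DLT rate exceeds one third is above 0.80, with a Beta(1/3, 2/3) prior. The prior and the cut-off are assumptions of this review. The smallest triggering counts k, by number of patients n, are:

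| k | 4 | 5 | 6 | 7 | 8 | 9 | 10 | 11 | 12 | 13 | 14 | 15 | 16 |
|---|---|---|---|---|---|---|---|---|---|---|---|---|---|
| by n | 8 | 10 | 13 | 15 | 18 | 21 | 23 | 26 | 29 | 31 | 34 | 37 | 38 |

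The exact recursion to n = 38 starts from 0/3 with weight w = (1−p)³/c(p), or from 1/6 with weight 1 − w, and checks after every patient:

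| p | 0.20 | 0.25 | 1/3 | 0.40 | 0.50 |
|---|---|---|---|---|---|
| Pauses | 1.7% | 5.5% | 23.7% | 49.8% | 85.8% |
| Mean n at pause or end | 37.6 | 36.8 | 33.6 | 28.9 | 20.6 |

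**5. Expected patients with a DLT among 38.** With no action at all this is w × 35p + (1−w)(1 + 32p). At p = 0.40, w = 0.698, giving 9.78 + 4.16 = 13.94.

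| | p = 0.40 | p = 0.50 |
|---|---|---|
| No action by anyone | 13.94 | 17.36 |
| Every pause ends enrolment | 10.30 | 8.65 |
| Same, 3 more patients enter first | 10.88 | 9.91 |
| Half of first pauses end enrolment, the rest run to 38 | (13.94+10.30)/2 = 12.12 | (17.36+8.65)/2 = 13.01 |

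**The case against.** **Oversight is already extensive.** A reader might infer that phase II runs without safety monitoring. The documents do not support that. Every toxicity comes before a biweekly meeting. At 1 to 3 patients a month, only about 0.5 to 1.5 patients enter between meetings, so the quarterly calendar is not the binding delay. Expedited review also reaches below grade 4: it covers unexpected grade 2–3 events of possible or stronger attribution, and grade 3–5 equivalents that cause hospitalization. The chair can act at once. All of this stands. What is absent is narrower: a count of all patients with a DLT, a number, and a required pause.

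**The benefit is measured against inaction.** This stands too. The figures without a rule assume that nobody intervenes through 38 patients.

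**The bad case is unlikely on one reading.** If phase II is one level below the MTD, a 40% level gets through 5–10% of the time and a 50% level 1.4–3.0%. The 31% and 17% figures need phase II to use the highest cleared level. The protocol contradicts itself on which applies, and that is a separate point.

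**The boundary is a preference, and a mild one.** Agreed. It misses about half of trials at a true 40%, and it applies to all patients a limit that Section 16 words per area. A boundary built on an acceptable rate of 20% would pause 87% of trials at 40%, at a 10% false-pause rate. That calculation starts from the first patient without conditioning on clearance, so it is not strictly comparable.

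**No sentence is false.** True; this is a weakness of design. A pause governs conduct while patients are entering, so it belongs in the protocol and cannot wait for an analysis plan.

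**Conclusion.** The point holds as a cheap improvement, not as an error that undermines the trial. Phase II has real and layered oversight. It lacks a pooled DLT count with a limit and a required pause.

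A reader might go further and conclude that a too-toxic dose would run unchecked to 38 patients. The documents do not support this: the CTMC can recommend suspension or closure, and it meets between quarters when safety requires. The reductions of 13.9 to 10.3 and 17.4 to 8.7 patients with a DLT are therefore upper bounds. They rest on existing oversight never acting, every pause ending enrolment at once, and true rates of 40% or 50% at a level that was nevertheless cleared. The rates, prior and cut-off are assumptions, since the protocol gives none for phase II. The finding that no rule counts or pauses depends on none of them.

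**What to change.** Add one paragraph to the Phase II part of Section 16:
- Count cumulatively, at each biweekly quality-assurance meeting, the phase II patients with a DLT by the Section 16 definition (30 days from the start of radiation). Include the phase I patients carried over.
- State that the Section 9.10 list governs individual Sutent dosing only, so that two DLT definitions do not compete.
- Pause enrolment for CTMC review when a pre-set boundary is met. The table in step 4 is one example, read as the 4th such patient by patient 8, the 5th by 10, and so on to the 16th by 38. The sponsor may choose an equivalent or stricter one.
- Leave the decision to resume with the CTMC.

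This uses existing meetings and data already collected, with no added patients or visits. With the example boundary, the price is an unneeded pause in 2% of trials at a true DLT rate of 20% and 5.5% at 25%. A stricter boundary would catch more bad doses and pause more often without need.
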